**Measurement and Data Collection Plan**

For Project 1, baseline questionnaire/interview data as well as physiological assessments will be collected during visits occurring prior to the quit day. This pre-quit data will also provide baseline data for Project 2. In addition to this baseline data, many of these same assessments will be collected at 12, 24, and 36 month (in-person) and 18, 30, and 42 month (telephone) follow-up contacts for Project 2. The timetable for data collected over the three years that comprise Projects 1 and 2 is depicted in Table 4.

*Annual In-Person Clinic Visits (Months 12, 24, and 36).* Participants enrolled in Project 2: Longterm Outcomes will attend an in-person clinic visit at one, two, and three years (12, 24, and 36 months) post-quit attempt. During these visits, participants will repeat many of the baseline assessments (see Table 4) including information to determine continuous and point-prevalence abstinence, the nature of any relapse event (environmental and social context, stressors, alcohol use, and so on), use of any new cessation aids, new quit attempts, and withdrawal and affective status (WSWS, PANAS, etc.). Suicidality will be assessed and appropriate referrals made in the event that suicide risk is determined.

Table 4 also lists other assessments that will take place at each annual in-person visit. Virtually all of the baseline paper-pencil questionnaires will be re-administered as well as the NCS-R-CIDI. In addition, some physiologic measures will be assessed including weight, body mass index, vital signs, waist circumference, and carbon monoxide (provided via a breath sample). Selected physical measures will be collected at some of these visits. For instance, the Carotid IMT, Exercise Stress Test, and NMR LipoProfile tests will be performed at the Baseline and Year 3 Visit. Brachial artery endothelial function will be tested at the Baseline and Year 1. Blood tests will completed at Baseline, Year 1 and Year 3 (but not Year 2) including NMR Lipoprofile, fasting glucose and insulin, hemoglobin A1C, creatinine, high sensitivity C-Reactive Protein, and possibly carotenoids.

The annual in-person clinic “visits” will occur over two days. The first day will involve assessment administration (questionnaires, simple physiologic measures). The second day will involve more complex physiologic measures including, when indicated, carotid IMT, brachial artery endothelial function, exercise treadmill stress test, and blood tests. Each of the two in-person Follow-up Visits days require about 2 hours (except for Year 2 when only a single day 2 hour visit is required). To ease the assessment burden we will take the following steps: (1) participants may interrupt the assessment session to take breaks, (2) there will be snacks to provide energy and a break from responding, (3) questionnaires may be completed at home if requested, and (4) participants may complete the assessments in multiple visits.

Pedometers will be distributed at the Annual Visits (months 12, 24, 36) along with a weekly recording log and a stamped, padded envelope addressed to the research center. Participants will be instructed to record the pedometer reading each night for a week and then return the pedometer by mail. Participants will receive a reminder phone call the day after they receive the pedometer to encourage daily recordings.

Assessments will be completed using the same procedures as at baseline. For instance, the NCS-R-CIDI will be administered in a computer-assisted format. If the participant is tested outside the research site, study personnel will administer it via laptop computer. Only the medical tests mandate an in-person visit. Finally, an additional visit will occur at 60 months after the quit day, but not within the funding period of this award. As in our previous research, responses on all forms will either be entered via computer (with “catch” criteria) at the time of collection or recorded on scannable forms to minimize the need for manual data entry. When scannable forms are used the researcher will inspect each form as it is completed to reduce scanning errors.

*Telephone Clinic Visits (Months 18 and 30).* A follow-up telephone assessment will take place at 18 and 30 months post quit-attempt. At this phone contact, the following factors will be assessed: continuous and seven day point-prevalence tobacco abstinence, the nature of the relapse contexts (environmental context, stress occurrence, use of alcohol, social context and so on), use of any cessation aids, new quit attempts, alcohol use in the last 7 days, tobacco withdrawal symptoms (WSWS), the PrimeScreen qualitative dietary survey, and affective status (PANAS) including suicidality. In total, this telephone assessment is estimated to take between 20 and 30 minutes.

**Measurement and Data Collection Plan - Assessments**

Physiologic

This research will target cardiovascular disease risk as the primary physiologic outcome of interest. This research will utilize state of the art, well-validated technologies and measures to prospectively assess atherosclerosis progression as well overall cardiovascular risk. Three of these measures (ultrasound measurement carotid IMT, brachial artery endothelial function, and advanced lipoprotein testing using NMR spectroscopy) are described below.

*Carotid intima-media thickness (Carotid IMT*). Carotid IMT quantifies sub-clinical atherosclerosis. This measure will be assessed at baseline and at the three year follow-up visit. Carotid IMT has been shown to provide specific predictive value for risk of heart attack and stroke and will be measured using the standardized protocol from the Atherosclerosis Risk in Communities (ARIC) study that optimizes images of the common, bifurcation, and internal segments of each carotid artery.225 The carotid arteries will be imaged with an 8.0 MHz linear array ultrasound transducer (8L5, Acuson Sequoia, Siemens Ultrasound). Images will be recorded and stored digitally using a Camtronics Vericis System (Camtronics Medical Systems, Hartland, WI) (Figure 2). The combined thicknesses of the intimal and medial layers of the far walls of each 10 mm carotid artery segment are measured in triplicate. Far wall mean and maximum wall thicknesses of each carotid segment are averaged to define a segmental mean or maximum Carotid IMT score. Composite Carotid IMTmax is calculated as the mean of the segmental maximum scores from all measurable segments (maximum of six). Composite Carotid IMTmean is calculated as the mean of the segmental mean scores from all measurable segments (maximum of six).226,227 In our laboratory, the coefficient of variation for Carotid IMTmax is 4.9% and Carotid IMTmean is 3.2%. These values imply a high degree of reproducibility, as good as or better than reported in major epidemiologic trials.20,23,225,228

*Brachial artery reactivity testing (BART):* Endothelial function will be assessed using ultrasound measurement of the brachial artery in response to flow mediated vasodilation (FMD). This dynamic measure of arterial function is impacted immediately by cigarette smoking and is extremely sensitive to rapid changes in risk factors for cardiovascular disease. This will be measured at baseline and at the one-year post-quit attempt visit. Impaired endothelial function is associated with cardiovascular risk factors and prevalent as well as incident cardiovascular disease including among smokers.229-233 This association is dose-dependent, both with increasing pack-years of exposure and varying levels of environmental tobacco smoke. It also seems to be potentially reversible as evidenced by the weaker association seen in former smokers.234 Further studies suggest a synergism between smoking and hypercholesterolemia,232 raising the possibility that smoking potentiates endothelial dysfunction by enhancing LDL oxidation.235,236

Brachial artery endothelial function will be measured noninvasively in the morning in the fasting state by a well-validated technique using high-resolution B-mode ultrasound of the brachial artery.235-239 Subjects who regularly use tobacco-containing products must refrain for 12 hours. After a 10-minute rest in a temperature-controlled room (68-70 F), the diameter of the right brachial artery blood flow are measured at baseline and in response to increased blood flow with a high-resolution (7.5 MHz) linear array vascular ultrasound transducer. Increased forearm blood flow, an endothelium-dependent vasodilator, is induced by inflating a pneumatic blood pressure tourniquet placed around the widest part of the forearm to a systolic blood pressure of 250 mm Hg., the release of which after 4.5 minutes leads to hyperemia. The change in brachial artery diameter in response to hyperemia relative to the baseline diameter defines FMD, which is described as a percentage change from baseline. A single-lead electrocardiogram is monitored throughout the study. Coronary and brachial artery flow-mediated vasodilation are correlated strongly (r=0.79, p<0.001).240 Endothelial function of the brachial artery also predicts future adverse cardiovascular events.235,236 In our laboratory, the coefficient of variation for FMD is 2.9% which compares favorably to that reported in the literature.241-243

*Advanced lipoprotein testing.* We intend to assess atherosclerotic risk and gain insight into observed changes in carotid IMT and endothelial function by assessing lipoprotein status using nuclear magnetic resonance (NMR) spectroscopy at baseline and during the three-year follow-up period of this grant. The NMR Lipoprofile (LipoScience, Inc. Raleigh, NC) provides a comprehensive assessment, including a large array of lipid sub-fractions that have been associated with atherosclerotic progression and cardiovascular events. Lipoproteins are also influenced by other factors associated with cessation such as weight gain and change in exercise rate.

Figure 3.Lipoprotein Subclasses Identified by NMR

Although total cholesterol levels are correlated with risk of cardiovascular disease, total cholesterol is not a good predictor of cardiovascular disease because cholesterol is a constituent of all major lipoproteins found in fasting plasma, including very-low density lipoproteins (VLDL), low-density lipoproteins (LDL), and high-density lipoproteins (HDL). Patients can have widely varying concentrations of these lipoproteins and have the same total cholesterol concentration.244,245 VLDL and LDL concentrations are associated positively with atherosclerotic vascular disease, whereas HDL concentrations are associated negatively with vascular disease. Lipoprotein metabolism is complex, however, and VLDL, LDL, and HDL each represent heterogeneous groups of particle subclasses that differ in size, lipid composition, and observed associations with cardiovascular disease.244-250

Advanced lipoprotein testing using NMR spectroscopy provides direct measurements of chylomicrons, VLDL, intermediate-density lipoproteins (IDL), LDL, and HDL and quantitative information about particle sizes (Figure 3).244,245,247 The NMR lipoprotein profile is necessary to interpret the physiological impact of metabolic changes and any changes in atherosclerosis progression and endothelial function that may be observed in this study. Recent data demonstrate that information about LDL particle concentration and LDL and HDL particle sizes improves cardiovascular disease risk prediction, even after controlling for standard lipid values.244-250 The limitations of standard enzymatic determinations of lipid levels are well known.244,245

The following methods will be used to determine NMR Lipoprofiles. After a 12 hour fast, approximately 2 cc of blood will be collected into a purple top EDTA specimen tube. This sample will be centrifuged immediately at 3000 rpm for 15 minutes. Plasma will be stored at -70C and shipped to LipoScience, Inc.. The technique LipoScience, Inc. uses to acquire and process the NMR data has been described in detail244,245,247 and consists of three steps: 1) acquisition, in duplicate, of the 400 MHz proton NMR spectra from the plasma specimen at 47C, 2) deconvolution of the lipid methyl group signal envelope appearing in the spectra at approximately 0.8 ppm, which yield the derived NMR signal amplitudes broadcasted by 16 modeled lipoprotein subclasses (Figure 4), and 3) conversion of the signal amplitudes into subclass concentrations using experimentally determined factors that relate the signal amplitudes of isolated subfraction standards to their chemically measured cholesterol and triglyceride concentrations. In general, large VLDL particles (V6, V5), IDL, small LDL (L1), and small HDL (H3, H2, H1) are considered atherogenic and associated with Metabolic Syndrome, as is an increased number of LDL particles.244,245,247

Figure 4.Relationship Between Plasma Lipid NMR Signal and Lipoprotein Subclasses

Carotid IMT, brachial artery enthothelial function testing and NMR lipoprofile testing will occur during Baseline of Project 1 (pre-quit). Because of the rapid changes in response expected for brachial artery endothelial function, it will be assessed again at one year post quit attempt. In contrast, carotid IMT will be assessed three years post quit when beneficial effects of cessation and detrimental effects of continued smoking are most likely to be seen. Finally, NMR Lipoprofile will be assessed at baseline, Year 1 and Year 3 post quit.

Other measures correlated with atherosclerotic risk will be assessed including blood pressure, weight, body mass index, heart and respiratory rate, creatinine, high-sensitivity C Reactive Protein, fasting plasma glucose and insulin, and hemoglobin A1C.

Physical Activity and Physical Fitness

*Physical activity*. This will be quantified using two methods: a physical activity questionnaire and pedometer measurements at baseline prequit, and at the ends of Years 1 & 3. The first is the International Physical Activity Questionnaire that covers all realms of physical activity (occupational, housework, etc.). This instrument has recently been shown to have acceptable reliability (Spearman’s rho = 0.80) and criterion-related validity (rho = 0.30), similar to other physical activity questionnaires.251 Questionnaires, however, tend not to be valid measures of moderate activity such as walking.252 Since walking is the most prevalent leisure-time activity in the U.S., is intrinsic to many daily routines, and is specifically mentioned in current nationwide physical activity recommendations253 it is particularly important to measure this specific activity. Pedometry has proven to be a very reliable and valid measure of steps walked when specific pedometer models are used.254

We propose to measure 7 days of walking annually with a Yamax Digiwalker SW-701. Subjects can be easily and quickly trained in the appropriate use of the pedometer and asked to fill out a simple log to record daily steps over the 7-day period.255 Through the use of both a simple questionnaire and a pedometer, we should be able to capture regular physical activity at targeted timepoints throughout the study.

*Physical fitness*. Each subject will have a symptom-limited treadmill test administered at baseline and at the 3-year follow-up.Peak oxygen consumption will be calculated from the final workload achieved on the test, and oxygen saturation (via pulse oximetry) will be measured at rest and continually during the test. The calculated oxygen consumption provides a measure of fitness, not physical activity, and is therefore a more objective measure than physical activity questionnaires and pedometry monitoring. This provides the opportunity to assess important changes in cardiorespiratory fitness associated with smoking cessation and physical activity.

While directly measuring oxygen consumption would provide a slightly more accurate assessment, the cost would be much greater. A modified Balke protocol will be used.256 Briefly, each subject will maintain a brisk walking pace and treadmill grade will be increased 2.5% every two minutes until volitional exhaustion. Oxygen saturation and 12-lead electrocardiogram (ECG) will be monitored continuously. ECG, heart rate, and blood pressure will be recorded at the end of each stage, maximum exercise, and every two minutes during recovery. The Borg scale rating of perceived exertion (RPE) ranging from 6 to 20 will be obtained near the end of each stage and maximum exercise. Differences will be compared between subject’s baseline prequit and three year follow-up tests for changes as they relate to smoking status. Changes in fitness based on these treadmill tests will be compared to other changes in the subject’s health status, including body weight, metabolic changes, and health outcomes.

Diet

Dietary factors will be assessed by a combination of a well documented food frequency questionnaire (FFQ), a qualitative screening food frequency questionnaire to track short-term changes, and objective biochemical indicators of diet (NMR Lipoproteins and, possibly, carotenoids).

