**Natural History of Smoking & Quitting: Longterm Outcomes**

**A. Specific Aims**

At present, some 50 million Americans smoke, these individuals are routinely encouraged to quit, and millions try to quit each year. A great deal is known about how quitting smoking affects a limited set of outcomes. For instance, it is well known that cessation affects the likelihood of lung cancer and heart disease. However, our knowledge of the effects of cessation is narrow. There are major gaps in our understanding of how cessation affects disease processes, mental health, psychosocial adjustment and life satisfaction. Also, little is known about the potential costs or adverse impacts of cessation. Finally, little is known about the precipitants of late relapse. The proposed research is aimed at addressing these gaps in our knowledge. Our cardinal goals are:

*1. To determine the effects of cessation and continued smoking on physiological mechanisms of cardiovascular disease*. We will use state-of-the-art assays such as carotid intima-media thickness, brachial artery endothelial function, and advanced lipoprotein testing to identify the mechanisms via which cessation leads to reduction of cardiovascular disease. We hypothesize that cessation will be followed by an arrest or reversal of atherosclerosis, but that this benefit will also be influenced by other modifiable risk factors (e.g., weight gain, diet, sedentariness, high stress). Our transdisciplinary assessment plan will allow us to produce new knowledge on the impact of cessation on atherosclerosis, and how cessation exerts its effects.1-8

*2. To determine the relation between cessation and mental health outcomes*. While cessation may exacerbate psychiatric symptoms in the short run (e.g., increased depression in the first year post-quit) we hypothesize that, over time, it will lead to decreased symptoms and a reduced likelihood of psychiatric diagnosis. These benefits may occur because smoking per se is a stressor9 because opponent-processes oppose the euphorogenic effects of nicotine10 or for other reasons. In sum we believe that our data will show that quitting smoking is the best thing that people can do to improve their mental health.

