All logistic regression models will be developed and tested using procedures and recommendations of Hosmer & Lemeshow.277 For instance, variable selection will start with a careful univariate analysis of each variable, and computation of smoothed scatterplots for continuous variables. After univariate analyses, all independent variables with P-values <0.25 will be candidates for multivariate analyses. Subsequent variable selection will occur in the context of forward selection with a test for backwards elimination. Subsequent to the identification of a multivariate logistic model, the performance of each variable will be evaluated via inspection of the Wald statistic, and the comparison of the multivariate and univariate errors and regression coefficients. If a new model is generated this will be compared with the larger former model via the likelihood ratio test. Eliminated variables will be re-entered to ensure that they have not become valid predictors through the exclusion of other variables. The performance of all continuous variables will be tested for linearity of the logit and any hypothesized (*a priori*) interactions tested. Model fit will be assessed via the Hosmer-Lemeshow test and via area under the ROC curve. Standard model diagnostics will be used (e.g., inspection of leverage values, variance of residuals for covariate patterns). Construction of multiple regression models will be similarly standardized and subjected to appropriate diagnostics.280

Model building will follow strategies frequently used in longitudinal research.1 Thus, *control variables* will be routinely entered (e.g., gender, age, site, ethnicity, Project 1 treatment, SES). Change will be modeled via entry of pretreatment (baseline) measures of the dependent variable and via change scores (which protect against interpretive biases of partialled scores.281,282 Next, relevant *individual differences* will be entered: e.g., nicotine dependence, personality, and genotypes, depending upon the analysis. Then other *modifiable risk factors* will be entered: i.e., measures of diet, alcohol use/abuse, weight/BMI/waist circumference, stressors/distress, exercise, blood pressure, serum lipids, and exposure to second hand smoke. Principal relations will be presented both in univariate and multivariate models. Two-way interactions to be tested will be based upon a priori hypotheses for each tested model.

*Principal Hypotheses*

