Hypothesis 1: Smoking cessation (amount of abstinence over the follow-up period coded either dichotomously or continuously) will be associated with *reversal or arrest of atherosclerosis* as assessed via CIMT. Baseline CIMT scores will be used to determine change. *Individual differences and control variables*: Progression will be greater among males283,284 and among those high in trait (MPQ) Negative Emotionality.2,4,8 The following *modifiable risk factors* will predict greater atherosclerotic progression: weight gain, fat intake,1 BMI, second-hand smoke, sedentariness, and high levels of stress (e.g., 5-7). Exercise/activity, however, will predict greater regression. Two critical interactions with smoking will involve second-hand smoke and gender since research suggests different impacts of smoking depending upon these variables.1,283

Hypothesis 2. Smoking cessation/reduction will be associated with positive changes in *mental health functioning* (from baseline status). Change will be measured from either baseline (lifetime) history of diagnosis, or baseline symptom levels, depending upon the analysis. While cessation may initially increase depression/depressive symptoms, long-term cessation will be associated with improved mental health status as reflected by lower rates of psychiatric diagnoses and reduced symptoms (thus, some analyses will focus on Year 2 and 3 symptoms/diagnoses). *Individual differences and control variables*: post-cessation symptoms will be positively related to trait (MPQ) Negative Emotionality and female gender (especially if diagnoses are restricted to internalizing disorders) and severity of prequit nicotine dependence. *Modifiable risk factors*: mental health symptoms/diagnoses will be inversely related to post-quit social support and physical health, and positively related to post-quit stressor occurrence and frequency of postquit heavy drinking days (relevant to dependent variables that do not themselves comprise alcohol diagnoses). No interactions are predicted for this family of analyses.

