## In the current study, we will use a more sensitive measure of carotid IMT (CIMTmax ) that averages segmental maximum carotid wall thicknesses from all measurable carotid artery segments (up to a maximum of six segments). Bots et al.288 recommended CIMTmax for intervention trials and also computed pooled estimates of the annual rate of CIMT change across multiple atherosclerosis trials. These pooled estimates were then used to compute sample size estimates for intervention trials. We use these same pooled estimates of CIMTmax change in power calculations for the current study. Other assumptions include: =.05, a 20% difference in CIMT progression between abstinent participants (N = 300) and continuing smokers (N = 450), and use of the CIMTmax measure with an estimated change in CIMT for continuing smokers of 5.28 m (SD= 5.0 m).288 Based on these assumptions, we will have power of .81 to detect a 20% difference in progression between abstinent and smoking participants. This is a conservative power estimate as control variables should reduce error and our N is likely to exceed 750, and the projected effect size is smaller than that reported by Howard et al.1 Thus, we believe that the current study is adequately powered to detect predicted differences in CIMT progression over three years for the comparison of smokers versus continuously abstinent ex-smokers. Analyses of continuous measures of post-quit smoking also may yield greater power.

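### The CIMTmax composite averages whichever segments are measurable, and change from baseline is not restricted to the same segments at both scans

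*Protocol*

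**What the plan says.** The carotid paragraph of the protocol's Measurement and Data Collection Plan - Assessments says that the imaging protocol "optimizes images of the common, bifurcation, and internal segments of each carotid artery". It defines the outcome as follows: "Composite Carotid IMTmax is calculated as the mean of the segmental maximum scores from all measurable segments (maximum of six"). On timing it says: "This measure will be assessed at baseline and at the three year follow-up visit".

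The Power section repeats the rule for the outcome on which power is computed, a measure that "averages segmental maximum carotid wall thicknesses from all measurable carotid artery segments (up to a maximum of six segments").

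The Analytic Plan forms change in two places. The general model-building text says: "Change will be modeled via entry of pretreatment (baseline) measures of the dependent variable and via change scores". Hypothesis 1 says: "Baseline CIMT scores will be used to determine change". The predicted result is that cessation "will be associated with *reversal or arrest of atherosclerosis* as assessed via CIMT".

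The protocol does not match segments across the two scans, set a minimum number of segments, adjust for segment type or say how to treat a segment seen at one scan only. The Analytic Plan's direct maximum likelihood method for missing data does not help. When a segment is lost the composite is still computed, so the model sees no missing value.

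**The concern.** A mean over a varying set of sites is comparable between visits only if the set stays the same or the sites have equal thickness. The definition itself allows for fewer than six segments. A participant with six segments at baseline and five at Year 3 has a change score that mixes true wall change with the difference between the lost segment and the rest. The same holds when a segment is gained.

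The effect sought is small, so a modest difference between segments matters for the individual change score. Two consequences are possible. Mismatch unrelated to smoking status inflates the variance of change and costs power. Mismatch whose pattern differs between abstainers and smokers would add a spurious component to the comparison that tests Hypothesis 1.

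**Working it through.** **Inputs from the Power section.** Smokers' change 5.28, SD 5.0 (the unit symbol is lost in the text; micrometres assumed), 20% difference, 300 abstinent and 450 smoking participants, alpha .05, stated power .81.

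**The plan's own figure.**
- Difference = 0.20 × 5.28 = 1.056.
- Standard error = 5.0 × √(1/300 + 1/450) = 0.373.
- 1.056 / 0.373 = 2.83. Two-sided power = Φ(2.83 − 1.96) = 0.809. The stated .81 reproduces.

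**Shift for one participant.** Let five segments have mean m and the sixth have thickness m + D. The six-segment composite is m + D/6 and the five-segment composite is m. Losing the sixth at Year 3 changes the score by −D/6. Losing it at baseline and regaining it changes the score by +D/6. If the segment is thinner than the rest, both signs reverse.
- D/6 = 1.056 gives D = 6.3, the planned group difference.
- D/6 = 5.28 gives D = 31.7, the whole assumed change in smokers.
- For assumed D of 50, 100, 200 and 400, the shift is 8.3, 16.7, 33.3 and 66.7.

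**Mismatch unrelated to smoking status.** Suppose a share q of participants lose one random segment and the between-segment SD is s. The added variance of change is q × s² × (1 + 1/5)/36 = q × s²/30, with mean zero. Adding it to 5.0² gives the following (s and q are assumptions):

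| s | q | SD of change | Power |
|---|---|---|---|
| 50 | 5% | 5.4 | 0.75 |
| 50 | 10% | 5.8 | 0.69 |
| 50 | 20% | 6.5 | 0.59 |
| 100 | 5% | 6.4 | 0.60 |
| 100 | 10% | 7.6 | 0.46 |
| 100 | 20% | 9.6 | 0.32 |

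**How common a mismatch could be.** If each segment had an assumed 5% chance of being unmeasurable at each visit, one segment would be mismatched with probability 2 × 0.05 × 0.95 = 0.095. At least one of six would be mismatched with probability 1 − 0.905⁶ = 0.45.

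**Mismatch related to smoking status.** A false difference of 1.056 requires the share losing such a segment to differ between the groups by 1.056/(D/6). That is 12.7, 6.3, 3.2 or 1.6 percentage points for D of 50, 100, 200 or 400.

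**A second benchmark for the noise.** The carotid paragraph gives a coefficient of variation of 4.9% for IMTmax. Assume this is per scan, four segments are at 700 and two bifurcation segments are thicker by g = 100 to 300.
- The composite is 700 + g/3 = 733 to 800, so the SD of a two-scan difference is √2 × 4.9% of that, about 51 to 55.
- Simulating 5% loss per segment and visit gives a spurious SD of 7.5 to 22.6.
- Total SD rises from 51 to √(51² + 7.5²) = 51.5, or from 55 to √(55² + 22.6²) = 59.5. That is about 1% to 8%.

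**The case against.** The strongest reply is that the protocol defines a score for one scan and never says that scores from different segment sets will be subtracted. A reading manual or an analysis plan not at hand may match segments. It is true that scan-by-scan measurability is the natural reading and not explicit wording. But the composite rule is fixed in the protocol, repeated for the powered outcome and linked to change from baseline without qualification. Followed as written, it permits the mismatch.

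A reader might infer that the artefact favours Hypothesis 1, because losing a thick segment at Year 3 looks like regression. The documents do not support that. Losing a thin segment at Year 3, or a thick one at baseline, looks like progression, and with equal loss rates at both visits the mean spurious change is zero. A reader might also suppose that weight gain after quitting degrades the images and so biases the contrast. The protocol describes the weight gain but does not connect it with image quality.

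The size is also open to challenge, and most of that challenge stands.
- Segment differences and loss rates come from outside the documents.
- The SD of 5.0 rests on pooled estimates from other trials and may already contain some of this noise, so the power losses above may be overstated. Against the 4.9% coefficient of variation, mixing adds little.
- The protocol describes the source estimates as annual rates. If 5.28 is annual, the three-year difference is 3 × 1.056 = 3.17 and the matching D is 19.0.

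Finally, a reader might infer that the planned contrast cannot show arrest or reversal, since abstainers at the planning values still thicken by 0.8 × 5.28 = 4.22. That is a separate matter. The protocol claims power only for a difference in progression, the 20% is a planning effect, and the abstainers' own mean change can be estimated from the two scans.

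**Conclusion.** The point holds as a badly fixed outcome definition. With six segments, one mismatched segment moves a participant's change score by D/6 in either direction with no true change, and D of about 6.3 matches the planned difference of 1.056. This follows by algebra from the stated rule, read scan by scan.

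For the trial as a whole, mismatch unrelated to smoking status adds noise and leaves the group contrast unbiased. Bias needs a change in measurability that differs by smoking status, which the documents neither show nor rule out. The total effect cannot be fixed from the protocol. Under the assumptions shown it runs from an increase of about 1% in the SD of change to a substantial loss of power, depending mainly on which noise benchmark is right. The correction is worth making because it is cheap and removes the question.

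**What to change.** State in the protocol that change in CIMTmax is computed only over segments measurable at both baseline and Year 3. Alternatively, fit a mixed model to the segment-level values, with segment and side as fixed effects and participant as a random effect, so that every measured segment contributes without altering what is compared. In either case, report the number and type of measurable segments at each scan by smoking status, so that differential loss can be seen.

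No new scans or participants are needed, because the composite is built from segment scores and the images are stored digitally. The cost is slightly more analysis work. The paired version also loses some precision where fewer than six segments are shared, and drops any participant with no segment in common.
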